**Methods:**

We will aim at children aged 8–13 years with problematic anxiety. We recruit these children via the community setting, and refer them to our online platform ‘Learn to Dare!’ (in Dutch: ‘Leer te Durven!’), https://leertedurven.ou.nl, where information about child anxiety and our research is freely accessible. After an active informed consent procedure, the participants can access the screening procedure, which will select the children with problematic anxiety levels. Thereafter, these children will be randomized to an online intervention based on Cognitive Behavioral Therapy (*n* = 120) or to a waitlist control (WL, *n* = 120). The intervention consists of 8 sessions with minimal therapist support and contains psycho-education, exposure (based on inhibitory learning), cognitive restructuring and relapse prevention. Child anxiety symptoms and diagnoses, cognitions, avoidance behavior and level of abstract reasoning are measured. Assessments are the same for both groups and are performed before and after the proposed working mechanisms are offered during the intervention. A follow-up assessment takes place 3 months after the final session, after which children in the waitlist control group are offered to take part in the intervention.

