Children in both groups perform the same assessments, which are all online within the ‘Learn to Dare!’ platform. Assessment points are aligned with the mediators, which means they take place before and after exposure and cognitive restructuring is offered to the children. At every assessment point child anxiety, avoidance behavior and dysfunctional cognitions are measured. The assessments are embedded in the intervention program, and take place after session 1 (after psycho-education and before the child’s expectancies are made explicit), after session 3 (before the start of actual exposures), after session 5 (before the start of cognitive restructuring), and at the end of the training. Control children receive automatically generated e-mails to notify them they have to complete an assessment. A follow-up assessment takes place 12 weeks after the last session. Both the intervention children and control children receive an automatically generated e-mail to notify they have to complete this assessment. At the follow-up assessment, the children take part in the diagnostic interview again. If children do not complete an assessment or intervention session, they will receive automatically generated reminders by e-mail twice. A research assistant also monitors the progress of the children and of the interviewers and trainers.

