Exposure is set up in line with the inhibitory learning model (described in: [40]). To accomplish this, we made the expectancy of the child about the feared situation explicit and aimed at applying variability during the exposure sessions. During session 2, the child is asked to step in an imaginary excavator to uncover the child’s anticipated negative outcome, or the child’s expectancy, of the feared situation. Participants are also encouraged to share the worst thing that might happen when confronted with their anxiety domain. The child’s expectations about the feared situation are tested during session 3, 4 and 5. For every one of his/her five expectations, the child indicates on a VAS scale how certain he/she is that the expectation will come true. We chose five expectations, to enable variation of testing situations, while keeping the number of testing situations feasible for an online early intervention. The trainer decides in which order these expectations will be tested. In accord with inhibitory learning, the order of exposures is not hierarchical, but rather starts off with a difficult experiment, to provide the child with a strong learning opportunity. The trainer also guides the child in minimizing the use of safety behavior and safety signals. During session 3, the child watches videos of other children preparing, performing and evaluating an exposure session based on inhibitory learning. Thereafter, the child chooses five rewards (e.g. getting to choose dinner, going to the cinema with mum/dad), one for every expectation he/she will test. Next, the child makes a first tracking plan, in which the child plans an experiment in which he/she will test the first expectation. In the tracking plan, the child describes how the expectation will be tested, where the expectation will be tested and who will assist the child. The child indicates on a calendar when this experiment will take place. Then, the child actually performs the experiment and shares the experience with the trainer. This can be done by uploading a movie clip or by describing the experiment in text or audio. After the exposure session, the child reflects on what happened during the exposure and on the possible non-occurrence of the anticipated negative outcome in the online workbook. The child reflects on the aspects of the expectation that were not correct, and completes another VAS scale indicating how certain the child is about the expectation after the experiment. The evaluation enhances the consolidation of the new learned association (CS – no US). During session 4 and 5, the child will design and complete the other four tracking plans.

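### The protocol contradicts itself on whether the second assessment (T2, after session 3) comes before or after the first exposure experiment

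*Protocol article*

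**What the plan says.** All places are in the protocol article.

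- **Abstract (Methods)**: assessments are the same in both groups and are "performed before and after the proposed working mechanisms are offered during the intervention".
- **Methods, Procedure**: "Assessment points are aligned with the mediators, which means they take place before and after exposure and cognitive restructuring is offered to the children". Five assessments follow: after session 1, after session 3, after session 5, at the end of training, and at follow-up 12 weeks after the last session. I take these to be the T1 to T5 of the Analyses section. The second is placed "after session 3 (before the start of actual exposures"); the third is placed before cognitive restructuring begins.
- **Methods, Intervention**: five expectations are to be tested ("We chose five expectations, to enable variation of testing situations"), and the "expectations about the feared situation are tested during session 3, 4 and 5". The account of session 3 opens with "During session 3, the child watches videos of other children preparing, performing and evaluating an exposure session based on inhibitory learning". It goes on to the choice of rewards, the first tracking plan and a calendar date, and then: "Then, the child actually performs the experiment and shares the experience with the trainer". The child's reflection and a second certainty rating come next. Only then does the text move on: "During session 4 and 5, the child will design and complete the other four tracking plans".

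**The concern.** The Background section on exposure and cognitive restructuring sets a condition for studying mechanisms: the outcome should change only once the active ingredient has been given. It says that this condition is rarely met. The trial's answer is the placement of its assessments before and after each ingredient, and T2 is the one named as preceding exposure.

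If one experiment has already been done by T2, a change seen between T1 and T2 cannot be read as change without exposure. The interval would hold the expectancy work of sessions 2 and 3 and one real experiment. That experiment need not be a minor one, because the Intervention section says that the sequence deliberately opens with a hard one. The aims at stake are the second to fourth: the efficacy of inhibitory-learning exposure, mediation through cognitions and avoidance, and the relative contribution of the two mechanisms.

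**Working it through.** The plan gives no figure to reproduce. The check sets the two sections side by side and counts experiments.

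**Inputs**
- Experiments planned: 5 (Intervention).
- Experiments in sessions 4 and 5: 4 (Intervention).
- T1 after session 1, T2 after session 3, T3 after session 5 (Procedure; labels mapped as above).

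**Count before T2**
- Intervention section: 5 − 4 = 1, and 1/5 = 20% of the experiments.
- Procedure section: 0, since exposure has not yet started.

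| Interval | Sessions | Experiments, per Procedure | Experiments, per Intervention |
|---|---|---|---|
| T1 to T2 | 2 and 3 | 0 | 1 |
| T2 to T3 | 4 and 5 | 5 | 4 |
| T1 to T3 | 2 to 5 | 5 | 5 |

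The first two rows differ and the third does not. The contradiction therefore concerns where T2 cuts the exposure block, not whether T1 and T3 enclose it.

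**A mixed case.** The child sets a calendar date for the first experiment, and nothing in the text ties T2 to that date. If a fraction p of intervention children have done the experiment by T2, the mean number before T2 is p × 1, anywhere from 0 to 1 of 5 (0% to 20%). The document gives no value for p. T2 would then mean different things for different children in the same arm.

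**From count to effect.** If the first experiment carries a share s of the total exposure effect, T2 to T3 holds 1 − s of it under the Intervention section. Only an assumption of equal, additive and immediate effects gives s = 1/5 and 1 − s = 80%. The document supplies no s, so 20% is a share of the count and not of the effect.

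**Where it enters the analysis.** The Analyses section regresses anxiety on group, sex and age category with group interactions. The mediators are modelled on group and linear time (0 to 4) with a random intercept, and anxiety is then modelled on group and both mediators. No T2-to-T3 contrast is specified. The position of T2 matters for the temporal-order argument, and for the planned exploration of other time codings that look for when an effect appears or fades.

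**The case against.** The best case on the other side is that the Procedure section is right and the Intervention section is loosely told. The note to Fig. 3 names session 3 for making plans, and the more active titles belong to sessions 4 and 5. The calendar step suggests that the experiment is scheduled for later. The trainer releases new parts of the programme and the assessments are embedded in it, so T2 could fall between plan and experiment. This stands as far as it goes: the document does not settle how sessions are delivered. It does not remove the conflict, because the Intervention section states outright that testing takes place in session 3 and leaves only four experiments for later.

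A reader might go further in four ways, none of which the document supports.

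- *T2 is certainly not a pre-exposure measurement.* That follows only if the Intervention section is the accurate one.
- *The T2-to-T3 estimate is biased by a known amount.* No such estimate is specified, and the share of effect carried by the first experiment is unknown.
- *The time order for mediation is broken.* Under either section T1 precedes all experiments, and T3 follows all of them and precedes cognitive restructuring. What may be lost is the separation of expectancy work from the first experiment.
- *The trial's efficacy result is compromised.* Both arms complete the same assessments, and the randomized comparison does not depend on what T2 is called.

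**Conclusion.** The contradiction is real and lies within the current text. T2 is preceded by no experiment according to the Procedure section and by one of five according to the Intervention section. It is more than a slip of wording, because the mechanism aims rest on assessments placed before and after each ingredient.

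The consequence is conditional. If the Intervention section describes delivery, T1 is the only assessment before any exposure, and T1 to T2 combines expectancy work with one experiment. The exposure and mediation aims then lose the pre-exposure point that the plan says it has, and phase-specific time codings become hard to interpret. The randomized group comparison and the T1-to-T3 bracket are intact. This should be fixed, but it does not threaten the main efficacy question.

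The conclusion assumes that T1 to T5 map onto the five assessments in the order listed.

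**What to change.** 1. Reconcile the Procedure and Intervention sections, and define T2 by its position relative to the first experiment rather than by session number alone.
2. If T2 is to remain the stated pre-exposure point, have the platform release it once the first tracking plan is written and before the first experiment is performed. Trigger the waitlist T2 at the matching time.
3. If T2 has already been taken after the first experiment, describe it that way and use T1 as the pre-exposure point for all children in both arms. Do not relabel T2 child by child. Whether a child has done the experiment by T2 is behaviour after randomization with no waitlist counterpart, so relabelling would give the wave different meanings within and between arms. The text also mentions only a planned date for the experiment, not a recorded date of performance.

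The cost is a wording correction and, under step 2, a change to one assessment trigger in each arm. No assessment is added and the content of the intervention is unchanged. Under step 3 the cost is a less fine division of the exposure period.

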### Intervention ‘Learn to Dare!’

The intervention ‘Learn to Dare’ is based on Cognitive Behavioral Therapy. The intervention focuses on the anxious children themselves and are provided on an individual basis. Parents are informed about the intervention’s content, and are asked to motivate the child to progress through the training. Children and parents also have to agree on the rewards children receive after the exposures. Parents do not function as layman-therapists. Every child is assisted through the online program by a personal trainer, who holds a bachelor in psychology. The trainers work via a detailed protocol and write personalized messages to guide the child via private messaging (PM). Adherence is stimulated by the parents’ and trainer’s encouragement. Trainers are instructed and supervised by the first author.

The intervention takes place on the ‘Learn to Dare!’ platform, where the child has his/her own online workbook (see Fig. 3), the child is encouraged to act like a detective, studying his/her own anxieties. The detective theme is apparent throughout the intervention. The trainer has access to the child’s workbook and controls whether children can progress or not with the training by releasing new parts of the intervention. The trainer also enters information in an automated progress sheet that functions on the background of the workbook and automatically inserts individualized texts in the child’s workbook. Neither interviewers nor other researchers have access to the child’s workbook.

**Fig. 3 Fig3:**
[figure not shown]
‘Learn to Dare’ intervention. *Note.* Sessions in consecutive order: 1. Getting to know each other, 2. Catching anxieties, 3. Making tracking plans, 4. Defy, 5. Dare, 6. Tracing thoughts, 7. Thought helpers, 8. Saying goodbye; Source of images: Simon, E., & Bögels, S. M. (2013). *Leer te durven! Werkboek*. Houten, Lannoo Campus. The first author has obtained written permission to use and adapt the figures for research purposes

At the start of the intervention, the trainer has to select two domains of anxiety that are targeted in the Learn to Dare program. These anxiety domains are selected by the following method: First, the trainer checks the SCID-Junior data to see if a DSM-5 classification exists for this child. If one or two classifications apply, these are selected to be targeted in the intervention (e.g. fear of heights; social anxiety). In case of more than two classifications, specific phobias are given priority over other anxiety disorders. In case of no DSM-5 classifications, the trainer checks the YAM-5 data and picks two types of anxiety, prioritizing specific phobias. The selected anxiety domains are entered in the system and will serve as targets in the intervention. The order in which the domains are targeted is randomized within the system, which means not the trainer but the system decides which anxiety domain will be targeted with exposure and which domain with cognitive restructuring. This minimizes chances of (unwanted) manipulation of the trainer (e.g. always target specific phobias with exposure and always target generalized anxiety with cognitive restructuring).

The intervention starts off with an introduction through messages between the trainer and the participant, and then psycho-education (session 1). In accord with the inhibitory learning model, exposure (session 2 to 5, see below) takes place before cognitive restructuring (session 6 and 7, see below). Because we chose to follow the inhibitory model, we could not randomize the order of exposure or cognitive restructuring over the participants. We, therefore, chose to target two anxiety domains, one for the working mechanism *exposure* and one for the working mechanism *cognitive restructuring*, and to randomize the order in which the domains are targeted. The first anxiety domain is targeted during exposure, the second domain during cognitive restructuring. This way, the net effect of the working mechanism on the child’s anxiety can be tested most validly while following the inhibitory learning model. The intervention ends with relapse prevention and saying goodbye to the trainer (session 8). Every week, one session takes place, except when the child wants to take a break during holidays.

Exposure is set up in line with the inhibitory learning model (described in: [40]). To accomplish this, we made the expectancy of the child about the feared situation explicit and aimed at applying variability during the exposure sessions. During session 2, the child is asked to step in an imaginary excavator to uncover the child’s anticipated negative outcome, or the child’s expectancy, of the feared situation. Participants are also encouraged to share the worst thing that might happen when confronted with their anxiety domain. The child’s expectations about the feared situation are tested during session 3, 4 and 5. For every one of his/her five expectations, the child indicates on a VAS scale how certain he/she is that the expectation will come true. We chose five expectations, to enable variation of testing situations, while keeping the number of testing situations feasible for an online early intervention. The trainer decides in which order these expectations will be tested. In accord with inhibitory learning, the order of exposures is not hierarchical, but rather starts off with a difficult experiment, to provide the child with a strong learning opportunity. The trainer also guides the child in minimizing the use of safety behavior and safety signals. During session 3, the child watches videos of other children preparing, performing and evaluating an exposure session based on inhibitory learning. Thereafter, the child chooses five rewards (e.g. getting to choose dinner, going to the cinema with mum/dad), one for every expectation he/she will test. Next, the child makes a first tracking plan, in which the child plans an experiment in which he/she will test the first expectation. In the tracking plan, the child describes how the expectation will be tested, where the expectation will be tested and who will assist the child. The child indicates on a calendar when this experiment will take place. Then, the child actually performs the experiment and shares the experience with the trainer. This can be done by uploading a movie clip or by describing the experiment in text or audio. After the exposure session, the child reflects on what happened during the exposure and on the possible non-occurrence of the anticipated negative outcome in the online workbook. The child reflects on the aspects of the expectation that were not correct, and completes another VAS scale indicating how certain the child is about the expectation after the experiment. The evaluation enhances the consolidation of the new learned association (CS – no US). During session 4 and 5, the child will design and complete the other four tracking plans.

Cognitive restructuring takes place during session 6 and 7, focusing on the second feared situation. During session 6, the child learns to detect dysfunctional thoughts and to replace dysfunctional thoughts by functional thoughts. In session 7, the child learns to use schemes that unravel anxious events into the four elements: neutral situation, anxious thought, anxious feeling, anxious behavior. The child gets acquainted with changing the dysfunctional, anxious thought within these schemes to a helping functional though, thereby positively affecting the child’s subsequent feelings and behaviors.

### Measurements

The measurement tools include questionnaires, an online task and an interview. The questionnaires and the online task are embedded in the ‘Learn to Dare!’ platform, and data are automatically entered into this platform. The diagnostic interview is performed by telephone by trained bachelors in psychology, who enter the data in a separate section within the platform. The diagnostic interviewers were never involved in providing the online CBT.

#### Child anxiety

##### Youth anxiety measure for DSM-5 (YAM-5, [54, 55])

The YAM-5 is a questionnaire that can be used to assess anxiety symptoms (or the anxiety level) in children and adolescents. This study focused on the child self-report version. The YAM-5 consists of two parts. Part I (28 items) taps symptoms of the major DSM-5 anxiety disorders, and thus contains the following subscales: separation anxiety disorder (6 items, e.g., I am afraid to go anywhere without my parents), selective mutism (4 items, e.g., At school, I don’t speak to the teacher at all), social anxiety disorder (6 items, e.g., I find it scary to meet new people), panic disorder (6 items, e.g., I panic for no reason), and generalized anxiety disorder (6 items, e.g., I worry about a lot of things). Part II (22 items) also contains 5 subscales covering the phobia types: animal (5 items, e.g., I am afraid of wasps), natural environment (4 items, e.g., I am afraid of the dark), blood-injection-injury (3 items, e.g., I am afraid of undergoing a small medical operation), other (4 items, e.g., I am afraid of people who are dressed up in costumes), and situational, which, in terms of fear content resembles agoraphobia (6 items, e.g., I am afraid when crossing a large town square). All items are rated on a 4-point Likert scale, ranging from 0 (never) to 3 (always). Good internal consistencies were demonstrated for the subscales of Part I and for the total scale of Part I and Part II. Furthermore, good test-retest reliability, good concurrent validity and good construct validity of both parts of the questionnaire were found.

##### Structured clinical interview for DSM-5 disorders for children (SCID, [56])

The SCID-junior is a structured clinical interview to assess the most common DSM-5 disorders in childhood, including all anxiety disorders. It is a DSM-5 modification of the Kid-SCID [57], a widely used interview for assessing DSM-IV childhood mental disorders that has moderate to good interrater reliability and internal consistency [58, 59]. The DSM-5 criteria for each disorder can be checked by a clinician, separately with the child, the parent(s), and other informants such as teachers, after which the clinician makes a “best judgment”.

#### Dysfunctional cognitions

##### Children’s automatic thoughts scale-negative/positive (CATS-N/P)

The CATS-N/P [60] is an extension of the CATS [61] and assesses negative (or: dysfunctional cognitions, DL’s) as well as positive thoughts in children. All of the items are scored on a 5-point scale, ranging from 0 (not at all) to 4 (all the time). The CATS contained the scales Physical Threat, Social Threat, and Personal Failure that measured negative thoughts. These subscales contain 30 items in total that can be added to form a sumscore, where higher scores reflect more negative thoughts. Positive thoughts are measured with the subscale Positive Thoughts that includes 10 items. These 10 items can also be added to form a subscore, with higher scores reflecting more positive thoughts. Hoogendoorn (2010) revealed good psychometric properties of the CATS-N/P, with total Cronbach’s alpha ranging between .90 and .96 for the total score and between .84 and .93 for the Positive Thoughts subscale.

